#### Assessing contextual factors and heterogeneity of intervention effects

To assess heterogeneity of intervention effects, ESCALATES will identify factors associated with substantial improvement for some practices and lack of change or worsening performance for others. For instance, the ESCALATES team may observe that practices receiving the external support strategy of data feedback/benchmarking resulted in significantly improved ABCS performance measures over time as compared to a group of practices receiving expert consultation or a control group of practices. On further analysis of the effect of type of practice (moderator) on the observed association, however, the ESCALATES team may find that practices affiliated with large health systems showed greater improvements in ABCS measures than independent practices. Thus, this effect modification analysis is designed to capitalize on the large sample size and diversity of practices and several different intervention strategies that will be tested by Cooperatives to identify heterogeneity of ABCS measures and practice capacity measures of association across levels of modifying variables. Another key variable of this analysis involves the fidelity with which practices implement QI tools to address ABCS. Data on implementation fidelity will be collected using the external support/practice implementation tracking data. ESCALATES will create meaningful categories of this variable to include in the modification analysis, such as practices that implement QI tools consistently and to a high degree of fidelity will likely perform better at improving ABCS and practice capacity than those that do not, even when both groups of practices receive the same external support.

This analysis will extend the DID models proposed above by testing individual moderators with a three-way interaction of intervention group, time point and potential moderator. Our choice of variables to include will be based on theory and on triangulation with qualitative findings. Potential moderators include practice characteristics, as significantly associated with ABCS outcomes at baseline, and contextual factors that emerge during implementation. Moderators may be identified through surveys or qualitative data. Moderators identified through qualitative data will be quantified whenever possible. In addition to testing individual moderators, we will consider a composite moderator, which may more strongly moderate the effect of the intervention strategies on ABCS outcomes than any single moderator. Specifically, ESCALATES will create a combined moderator that is developed as a weighted combination of individual selected moderators to identify for which practices different intervention strategies may be preferred. Combining moderators has been shown to exhibit a larger moderator effect size than any individual moderator [67]. We will develop and evaluate a composite moderator using the parametric approach developed by Kraemer [69], which constructs a composite moderator from a weighted average of moderators that are weighted to maximize the correlation between the outcome difference between randomly paired practices and the average of the two values of the moderator variable.

In addition to these quantitative analyses of heterogeneity, we will also conduct qualitative analyses to evaluate the multilevel contextual factors that could affect either the interpretation of the results of each analysis, or that might be useful for others attempting to replicate or reinvent interventions in different times or situations [70, 71]. These analyses will use multiple data sources across multiple levels (from the practice and health care system, the intervention/evaluation team, and the local and national policy context), and will attempt to include diverse stakeholder perspectives of the most important contextual factors at critical points in the project/intervention, to help understand what happened here and why, and what someone else would need to know to transport/re-invent what was learned here in a different time and place. These analyses will enhance the external validity of ESCALATES findings.

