Stratified ABCS measures	Proportion of patients stratified by gender, age, race, ethnicity, insurance type meeting ABCS	Aggregated by practice	Medical record (EHR extraction); collected by Cooperatives; shared with ESCALATES	Quantitative	Baseline through end of study; Quarterly
Practice survey	Practice capacity (CPCQ), EHR adoption, practice demographics (internal and external characteristics)	Practice-level	Survey (online/paper); completed by office manager or designated clinic leader; collected by Cooperatives; shared with ESCALATES	Quantitative	Baseline, post-intervention, 6 m follow up
Practice member survey	Practice capacity (AR), focus on patients’ needs and resources, practice readiness to change, burnout, clinician attitudes towards new guidelines	Aggregated by Practice	Survey (online/paper) completed by a majority of practice members (target > 70 %); collected by Cooperatives; shared with ESCALATES	Quantitative	Baseline, post-intervention, 6 m follow up
External support intervention tracking	Type of external support provided, date of contact, mode of contact, duration of contact, practice engagement assessment	Practice-level	Collected by Cooperatives; shared with ESCALATES	Quantitative	Regular intervals; TBD by grantees and evaluation
Practice implementation intervention tracking	Strategies in place to improve ABCS, assessment of the extent to which strategies are implemented	Practice-level	Collected by Cooperatives; shared with ESCALATES	Quantitative	At least baseline and post-intervention
Practice site visits	To observe and understand how interventions are implemented	Cooperative-level	Fieldnotes	Qualitative	60 practice site visits across years 2 and 3
Patient pathways	To observe patients exposure to/experience with intervention	Practice-level	Observation by evaluation team during site visits	Qualitative	Observe five–ten patient visits at each practice visit
Context assessment	To understand the contextual factors of implementation	Cooperative-level	Interviews with Cooperative key stakeholders	Qualitative	Annually with two–three people or as needed

**Table 2 Tab2:** Key elements of the ESCALATES evaluation

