#### External support and practice implementation tracking

It is important for this evaluation to track characteristics of the interventions delivered to practices, including the type and intensity of external support interventions received, along with changes that practices implement to increase ABCS delivery. The ESCALATES team will work with Cooperatives to establish methods (e.g., practice facilitator contact logs, collaborative (onsite) or webinar attendance records) to track the type, frequency, duration and mode of external support provided to practices and their engagement with it. Data collection related to external support will continue throughout each Cooperative’s active intervention period, which will vary by Cooperative. The ESCALATES team will also work with Cooperatives to develop mutually agreeable methods to track and share the change strategies practices implement to improve ABCS (e.g., registries, standing orders) and the extent to which these changes are implemented within these practices.

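### Implementation fidelity, and emergent factors that support can affect, are tested as effect moderators although they arise after support starts, so the interaction and stratum effects are open to bias

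*Protocol article*

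**What the plan says.** The section on contextual factors and heterogeneity of intervention effects makes fidelity a key variable of the effect-modification analysis ("Another key variable of this analysis involves the fidelity with which practices implement QI tools to address ABCS") and adds that "ESCALATES will create meaningful categories of this variable to include in the modification analysis". Its source is given: "Data on implementation fidelity will be collected using the external support/practice implementation tracking data".

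The timing of those data is in two other places. Under the heading on external support and practice implementation tracking, "Data collection related to external support will continue throughout each" Cooperative's active intervention period. In Table 1, practice implementation tracking ("Strategies in place to improve ABCS, assessment of the extent to which strategies are implemented") is collected "At least baseline and post-intervention".

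The heterogeneity section extends the difference-in-differences (DID) model by "testing individual moderators with a three-way interaction of intervention group, time point and potential moderator". The candidate list reads: "Potential moderators include practice characteristics, as significantly associated with ABCS outcomes at baseline, and contextual factors that emerge during implementation". Selected moderators may then be weighted into one composite, whose stated purpose is to show which practices may be better served by which strategy.

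Nothing in the article limits moderators to values fixed before support starts, and nothing separates moderators from mediators.

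**The concern.** A variable can be read as an effect modifier only if the intervention does not influence it. Fidelity does not meet this condition on the protocol's own account. The research questions ask what the strategies do to practice processes, and the section on change in outcomes plans to estimate differences in practice implementation between strategies. The same construct is thus both a result of support and a moderator of its effect.

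Practices that reach high fidelity with support and practices that reach it unaided are likely to differ in leadership, stability and motivation, and those traits may also drive ABCS improvement. Comparing arms within a fidelity stratum then compares different kinds of practice. The planned practice fixed effects remove stable differences in level, but not differences in the tendency to improve, which is the confounder here.

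Two readings are at stake: that support works better, or only, in high-fidelity practices; and that the composite can guide who should receive which strategy. A factor unknown before support starts cannot serve the second purpose, whatever its statistical association.

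**Working it through.** The protocol gives no SD, correlation, effect size or power figure for this analysis, so there is nothing to reproduce. The check asks whether the three-way term and the stratum effects can depart from the truth, and in which direction.

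**Set-up.** The only input from the documents is about 1,500 practices. The rest is assumed:
- The pre-to-post change is dY = 0.05·I + g·U + e, where I is support (half the practices), U is a standard normal unmeasured tendency to improve, and e has SD 0.10. The true effect is 5 points in every stratum, so the true three-way interaction is 0.
- High fidelity (M = 1) occurs when a + b·U + noise > 0. The threshold a is set so that a share p of the arm has high fidelity. The link b and the share p may differ between arms (b0, p0 without support; b1, p1 with it).

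**Formulas.** Let r = b/√(1+b²) and let φ be the normal density at the p-quantile. Within an arm, mean U is r·φ/p among high-fidelity practices and -r·φ/(1-p) among low-fidelity practices. Then:
- stratum effect = 0.05 + g × (mean U with support - mean U without support, in that stratum);
- three-way term = effect in the high stratum - effect in the low stratum.

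**One case in full.** Take p0 = 0.2, b0 = 0.3, p1 = 0.6, b1 = 1, g = 0.05.
- Without support: r = 0.2873, φ = 0.2800. Mean U is 0.2873×0.2800/0.2 = 0.402 (high) and -0.2873×0.2800/0.8 = -0.101 (low).
- With support: r = 0.7071, φ = 0.3863. Mean U is 0.7071×0.3863/0.6 = 0.455 (high) and -0.7071×0.3863/0.4 = -0.683 (low).
- High stratum: 0.05 + 0.05×(0.455 - 0.402) = 0.053. Low stratum: 0.05 + 0.05×(-0.683 + 0.101) = 0.021. Three-way term: 0.032.

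**Simulation.** 1,500 practices, 1,000 replicates, robust standard errors, two-sided 5% test. Results are in percentage points; the truth is 0 for the three-way term and 5 for each stratum.

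| Case | Three-way | Effect, low / high | Rejection |
|---|---|---|---|
| M unaffected by support, tied to U (p 0.5, b 1 in both arms) | +0.1 | 5.0 / 5.0 | 5.1% |
| M raised by support (0.2 to 0.6), not tied to U | +0.1 | 5.0 / 5.0 | 5.1% |
| M raised 0.2 to 0.6, b 0.3 vs 1, g 0.05 | +3.2 | 2.1 / 5.3 | 67.4% |
| Same, g 0.02 | +1.3 | 3.8 / 5.1 | 19.0% |
| M raised 0.2 to 0.6, b 0 vs 1, g 0.05 | +5.8 | 1.5 / 7.3 | 99.2% |
| M raised 0.05 to 0.5, b 1 in both arms | -2.1 | 2.6 / 0.6 | 19.5% |
| M raised 0.2 to 0.6, b 1 in both arms | -0.5 | 2.8 / 2.3 | 6.4% |
| M raised 0.2 to 0.8, b 1 in both arms | 0.0 | 1.3 / 1.3 | 4.2% |

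The simulated +3.2 agrees with the 0.032 worked by hand.

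**Reading.** A moderator that support does not affect is safe in this model even when it predicts improvement. Trouble starts when support shifts the variable and it also shares a cause with the outcome. The interaction may then be positive, negative or null. In the null case the stratum effects are still far from 5.

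**The case against.** Several objections have weight.

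- **Scope.** The protocol evaluates strategies as assigned and calls the fidelity work sub-analyses within a declared observational study. A reader might infer that the main DID effect is compromised. It is not, because it does not condition on fidelity. Interactions with baseline practice characteristics, such as the article's example of health-system affiliation, are untouched too.
- **Emergent does not mean caused by support.** Outside policy or incentive changes can arise during implementation without being consequences of it. The concern covers only emergent factors that support can affect.
- **The fidelity hypothesis is partly within-support.** The article's illustration compares practices given the same external support, so non-comparable controls do not enter that contrast. Self-selection into high fidelity still does, and the contrast is then an association, not effect modification.
- **Size.** It is tempting to size the bias from a median split: 1.596 SD × a correlation of 0.1 to 0.3 × an assumed SD of 10 points gives 1.6 to 4.8 points. That is a high-versus-low difference in change within an arm. If it is equal in both arms it cancels from the three-way term, so it does not measure bias in that term.
- **Choice of moderators.** A reader might also infer that requiring a significant baseline association screens out true modifiers. The text does not support this. It bases the choice on theory and triangulation with qualitative findings, and its list of candidates is not exclusive.

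These objections narrow the point. They do not remove it: fidelity is explicitly placed in the modification analysis, and no text restricts how the result may be read.

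**Conclusion.** The point holds in limited form. Fidelity, and any emergent contextual factor that support can affect, should not be tested or interpreted as an effect moderator in the three-way DID model, and should not enter the composite. The estimates are open to bias; the documents do not show that they are biased by a known amount. Under the assumptions above (true effect 5 points, residual SD of change 10 points, U effect 2 to 5 points), the three-way estimate ran from -2.1 to +5.8 points and false rejection from 4.2% to 99.2% in the cases where fidelity was both raised by support and tied to U. The large positive values need a link to improvement tendency that is stronger, or present only, in supported practices. If fidelity shares no cause with ABCS improvement, the problem disappears in this model, but the protocol gives no basis for assuming that.

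The point about the composite needs none of these assumptions. A variable known only after support starts cannot tell a funder which practices to assign to which strategy.

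**What to change.** In the heterogeneity section, restrict the three-way moderator tests and the composite to variables measured before support starts, or clearly external to the intervention, such as outside policy changes. The baseline round of practice implementation tracking in Table 1 may be used as a baseline characteristic. It describes strategies already in place and does not stand in for fidelity during implementation.

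Analyse post-start fidelity in one or more of three ways: as an outcome of support; in a mediation analysis with its assumptions stated; or as a descriptive association among supported practices that is not labelled effect modification. Handle emergent factors that support could have influenced in the same way.

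No new data collection is needed. The cost is that fidelity conclusions become weaker: whether support works better where fidelity is high is no longer answered by an interaction test, and a mediation analysis would rest on assumptions that cannot be fully checked.

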
#### Effect of intervention strategies on change in outcomes

Examining the effectiveness of external support interventions will involve estimating differences in ABCS and practice capacity outcomes for different intervention strategies received by practices engaged in each Cooperative, as well as differences in practice implementation. Intervention strategies will be compared to each other and/or to a control group of practices using a differences-in-differences (DID) approach [62]. The DID model is a flexible approach which can accommodate different study designs Cooperatives may propose to evaluate their own interventions. Conceptually, cluster-randomized designs, interrupted time studies, and step-wedge designs can be nested within the DID framework. The primary requirements are the inclusion of baseline (pre-intervention) data and data from a control group. In addition to examining the effectiveness of intervention typologies as assigned, we will also conduct sub-analyses that include differing levels of fidelity to quality improving strategies practices use. The DID approach has been frequently used by health services researchers and economists to account for potential secular effects and changing policies that would affect both intervention and control groups over time, while adjusting for potential confounders [7, 63–68].

The overall analysis to assess intervention strategies on ABCS performance can be considered as shown in the equation$$ {\boldsymbol{Y}}_{\boldsymbol{it}}=\boldsymbol{f}\left(\boldsymbol{\alpha} +{\displaystyle \sum_{\boldsymbol{j}=1}^{\boldsymbol{r}}}{\boldsymbol{\beta}}_{\boldsymbol{j}}{\boldsymbol{I}}_{\boldsymbol{j}}+\boldsymbol{\delta} {\boldsymbol{\tau}}_{\boldsymbol{j}}+{\displaystyle \sum_{\boldsymbol{j}=1}^{\boldsymbol{r}}}{\boldsymbol{\theta}}_{\boldsymbol{j}}{\boldsymbol{I}}_{\boldsymbol{j}}{\boldsymbol{\tau}}_{\boldsymbol{j}}\right), $$

where: ***Y***
_***it***_ represents clinic *i’*s performance on an outcome measure (i.e., one of the ABCS measures, mean adaptive reserve score) at time *t*,; ***I***
_***j***_ represents a dummy variable (intervention strategy received variable described above) taking a value of 1 if the clinic was involved in intervention *j* and zero otherwise; and ***τ***

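### Implementation fidelity, tracked as an extent over several strategies, is to be grouped for the effect-modification analysis; two or three groups would lose about 20% to 50% of the linear information in a roughly normal score

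*Protocol article*

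**What the plan says.** The commitment is in the section on contextual factors and heterogeneity of intervention effects. After naming fidelity a key variable, the article says: "ESCALATES will create meaningful categories of this variable to include in the modification analysis". The illustration expects practices that use the QI tools consistently and faithfully to improve more "than those that do not, even when both groups of practices receive the same external support". That is a contrast of two groups. The number of categories and the cut-points are not given, and no analysis of fidelity as a graded quantity is mentioned.

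The same section gives the source: "Data on implementation fidelity will be collected using the external support/practice implementation tracking data". Table 1 (under Study design) describes the practice implementation tracking as "Strategies in place to improve ABCS, assessment of the extent to which strategies are implemented". The section on external support and practice implementation tracking speaks of "the extent to which these changes are implemented within these practices", with registries and standing orders as examples of the changes. It also says that the team will work with Cooperatives to "develop mutually agreeable methods to track and share the change strategies practices implement to improve ABCS", so the instrument was not settled when the article was written.

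Moderators enter the difference-in-differences model through a three-way interaction of intervention group, time point and moderator.

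**The concern.** An extent recorded over several strategies would usually yield more than two levels per practice, whether as a sum, a mean or a set of ordered ratings. Grouping it treats all practices within a band as alike and treats those on either side of a boundary as different by the full step. If the true relation is gradual, the model then explains less of it.

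This matters most where precision is already weakest. A three-way interaction is estimated less precisely than a main effect, and the article says this analysis is meant to exploit the large and diverse sample. Coarse grouping works against that aim. The likely consequence is that real moderation by fidelity is missed or described too crudely.

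The article states this as a choice about how the variable enters the model. It is not a detail merely left to an analysis plan.

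**Working it through.** **Is there a figure to reproduce?** No. The article gives no power, significance level or effect size for this analysis, so the check is of the information lost by grouping.

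**Inputs from the article.** Fidelity is to be categorised and the example has two groups (heterogeneity section). The source is an extent over several strategies (Table 1 and the tracking section).

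**Assumptions not in the article.** The score is roughly normal, moderation is linear in the score, the cuts are placed as listed below, and tests are two-sided at 5%.

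**Formula.** For a standardised score cut into groups with shares p_k and group means m_k, the share of linear information retained is R = Σ p_k m_k². For two groups cut at z, with share p on one side, this becomes R = φ(z)² / [p(1 − p)].

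**Normal score**

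- Median split: z = 0, φ = 0.3989. R = 0.3989² / 0.25 = 0.637 (that is, 2/π). Loss 36%.
- Three equal groups: cuts at ±0.431, φ = 0.3636. The outer group means are ±0.3636 / (1/3) = ±1.091 and the middle mean is 0. R = (2/3) × 1.091² = 0.793. Loss 21%.
- 20/80 split: z = 0.842, φ = 0.280. R = 0.280² / 0.16 = 0.490. Loss 51%.
- Outside that range: four equal groups R = 0.861 (loss 14%), five equal groups R = 0.897 (loss 10%), 10/90 split R = 0.342 (loss 66%).

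**Other scales**

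| Score | Three equal groups | Median split |
|---|---|---|
| Uniform | 11% lost | 25% lost |
| Exponential (skewed) | 35% lost | 52% lost |

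- An ordinal item with 3 to 5 evenly used levels, cut into two groups, loses 20% to 50% depending on the cut. For example, levels 0, 1, 2, 3 have variance 1.25. Splitting in the middle gives group means 0.5 and 2.5 and a between-group variance of 1, so R = 1 / 1.25 = 0.80.
- An ordinal item whose own levels are kept as the categories loses nothing.

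**What this means for power.** Suppose a test on the graded score had 80% power. With grouping, power is Φ[(1.960 + 0.842) × √R − 1.960].

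- Three equal groups: 2.802 × 0.891 − 1.960 = 0.535, power 70%.
- Median split: 2.802 × 0.798 − 1.960 = 0.275, power 61%.
- 20/80 split: 2.802 × 0.700 − 1.960 ≈ 0, power 50%.

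These power figures show the order of magnitude for a linear term. They were not derived for the three-way interaction in the planned beta-regression model.

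**The case against.** The strongest reply is that the article never says fidelity is a graded score. It gives no scale, and the tracking methods were still to be agreed with the Cooperatives. The record could be a checklist or a few ordered ratings, and making categories could simply mean building one usable variable from differing logs. If the categories are the tool's own levels, nothing is lost. The example may illustrate a hypothesis and need not fix a two-group split. The Limitations section also expects that measures may not be fully harmonised across Cooperatives, and broad categories can then be a defensible common denominator. All of this stands. It makes the loss conditional and limits where the remedy can be used. It does not remove the fact that the only stated plan is to categorise something described as an extent, with no graded analysis beside it.

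A reader might infer three stronger things that the article does not support.

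- **That the cut-points will be chosen after the results are seen.** The article is silent on timing. The Trial status section shows measures still being refined ahead of baseline collection, and cut-points are commonly left to an analysis plan.
- **That the same fault affects the planned "sub-analyses that include differing levels of fidelity to quality improving strategies practices use".** That wording, in the section on the effect of intervention strategies, does not commit to grouping a score.
- **That the loss equals a fixed number of the roughly 1,500 practices.** That total is an upper limit, since drop-out and missing data are expected. The conversion would also carry a simple linear result into a more complex model.

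**Conclusion.** The point holds as a conditional, minor improvement. The article plans to categorise a key moderator that it describes as an extent over several strategies, and its illustration uses two groups. If the tracked extent gives a roughly normal score related linearly to the effect, two or three groups would lose about 20% to 50% of the linear information: 21%, 36% or 51% for the three cuts worked through above. That range is not a bound. It depends on the scale, the distribution, and the number and placement of the groups, none of which the article states.

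It would be wrong to say flatly that the plan discards a fifth to a half of the information. What is at stake is the precision of one moderator analysis. The main difference-in-differences estimates do not change.

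**What to change.** In the heterogeneity section, replace the commitment to categories with wording to this effect: in the three-way interaction, fidelity enters as the recorded score (linear, with a spline as a check on shape) or, if the tool is ordinal, as all its recorded levels with a trend term, wherever the tracking data are comparable across Cooperatives. Collapsed categories are used only to display results, or where differences in tracking make a common score impossible. As a safeguard, define any such categories from the tracking tool before linking to the ABCS outcomes.

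The cost is a sentence or two of analysis wording and slightly less simple presentation. The real requirement is a common metric across Cooperatives, which the article does not promise. It could be sought while the tracking methods are still being agreed.
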